### Aim 2: Develop an Algorithm to Explain Prediction Results and Suggest Tailored Interventions

For patients with predicted risk greater than a predetermined threshold, such as the 95th percentile, this aim will explain prediction results and suggest tailored interventions. These explanations and suggestions can help clinicians make final decisions on the management levels and interventions for these patients.

Prediction accuracy and model interpretability are frequently 2 conflicting goals. A model achieving high accuracy is usually complex and difficult to interpret. How to achieve both goals simultaneously has been a long-standing open problem. Our key idea to solve this problem is to separate prediction and explanation by using 2 models concurrently, each for a different purpose. The first model makes predictions and targets maximizing accuracy. In this study, this model is the best one built for the outcome variable in Aim 1. The second model is rule-based and easy to interpret. It is used to explain the first model’s results rather than make predictions. The rules used in the second model are mined directly from historical data rather than coming from the first model. For each patient whom the first model predicts to be at high risk, the second model will show zero or more rules. Each rule gives a reason why the patient is predicted to be at high risk. Because some patients can be at high risk for rare reasons that are difficult to identify, we make no attempt to ensure that at least one rule will be shown for every patient predicted to be at high risk. Instead, we focus on common reasons that are more important and relevant to the patient population than rare ones. We expect most high-risk patients to be covered by one or more common reasons.

We will use an associative classifier [83-85] from the data mining field as the second model. Associative classifiers can handle both numerical and categorical variables and be built efficiently from historical data. Compared with several other rule-based models, an associative classifier includes a more complete set of interesting and useful rules and can better explain prediction results. For ease of description, our presentation focuses on the case that each patient has exactly one data instance (row). The case in which a patient has more than one data instance can be handled similarly. We will proceed in 3 steps.

In step 1, association rules are mined from historical data. As mentioned in Aim 1, each patient is described by the same set of patient, physician profile, and environmental variable features and labeled as either high risk or not. An associative classifier includes a set of class-based association rules. Each rule includes a feature pattern associated with high risk and is of the form: *p*
_
*1*
_ AND *p*
_
*2*
_ AND ... AND *p*
_
*k*
_ is associated with high risk. The value of *k* varies across different rules. Each item *p*
_
*i*
_ (1≤*i*≤*k*) is a feature-value pair of the form (*f*, *v*) indicating that feature *f* takes a value equal to *v* (if *v* is a value) or within *v* (if *v* is a range). The rule suggests that a patient is likely to be at high risk if he/she satisfies *p*
_
*1*
_, *p*
_
*2*
_, ... , and *p*
_
*k*
_. An example rule is the patient was hospitalized for asthma last year AND the patient’s primary care physician has fewer than 10 asthma patients is associated with high risk.

For a given association rule, the percentage of patients satisfying the rule’s left side and being at high risk reflects the rule’s coverage and is called the rule’s *support*. Among all patients satisfying the rule’s left side, the percentage of patients at high risk reflects the rule’s accuracy and is called the rule’s *confidence*. An associative classifier includes association rules at a given level of minimum support (eg, 1%) and confidence (eg, 70%). These rules can be efficiently mined from historical data using existing techniques [83-85], which can eliminate redundant and noisy rules. Because we need only rules suggesting high risk, we can mine desired feature patterns (ie, the rules’ left side) from high-risk patients’ data rather than from all patients’ data to improve the efficiency of rule generation.

Typically, many association rules will be mined from historical data [83-86]. Keeping all these rules will overwhelm clinicians. To address this issue, we will use 3 methods to reduce the number of rules. First, in forming rules, we will consider only features appearing in the first model that is used to make predictions. As mentioned in Aim 1a, many nonessential features will be removed during feature selection and backward elimination when building the first model. Second, we will focus on rules with no more than a predetermined small number of items (eg, 4) because long feature patterns are difficult to understand and act on [83]. Third, users can optionally specify for a feature what values or type of range (eg, stating that the feature is above a threshold) may potentially indicate high risk and appear in rules [40,87]. The other values or types of range are not allowed to appear in rules. This also helps form clinically meaningful rules.

In step 2, interventions will be listed for the mined association rules. Through discussion and consensus, our clinical team will examine mined association rules and remove those that make little or no clinical sense. For each remaining rule, the clinicians will list zero or more interventions addressing the reason given by the rule. Example interventions for patients include (1) provide transportation or telemedicine for a patient living far from his/her physician, (2) schedule longer or more frequent doctor appointments for a patient with multiple comorbidities, (3) schedule appointments with nurse educators or clinical pharmacists for a patient with multiple comorbidities, (4) arrange language service for a doctor appointment if the patient and physician speak different languages, and (5) give wearable air purifiers to certain types of asthma patients living in an area with bad air quality.

Example interventions at the system level include (1) provide the primary care physician continuing medical education on a specific disease, cultural competence, women’s health, or pediatric health if he/she is unfamiliar with or cannot well manage the disease, patients of a particular race, diseases in women, or pediatric diseases (a physician may be unfamiliar with a disease if he/she has few patients with it; a bad mean outcome of a physician’s patients with the disease may indicate, but not always, that the physician cannot manage the disease well); (2) extend physician office hours; and (3) open a new primary care clinic in an area with no such clinic nearby.

Interventions for patients are displayed to clinicians in step 3. Interventions at the system level are optional and may be viewed only by managers of the health care system. We call a rule actionable or nonactionable based on whether or not at least one intervention is associated with it. The remaining rules and their associated interventions will be stored in a database to facilitate reuse.

In step 3, prediction results are explained and tailored interventions are suggested. At prediction time, for each patient identified as high risk by the first model, we will find all association rules whose left side is satisfied by the patient using an index for rules [84]. We will display the actionable rules above the nonactionable ones, each in descending order of confidence [84]. If 2 rules have equal confidence, the rule with higher support will be ranked higher. If 2 rules have the same confidence and support, the one with fewer items will be ranked higher. Our rule sorting method differs from several traditional ones [83-85] because our goal is to explain the prediction result for a patient rather than to maximize the average prediction accuracy in a patient group. We will list confidence and associated interventions, if any, next to each rule to help the clinician identify suitable tailored interventions. By default, we will show no more than a predetermined small number of rules (eg, 3). If desired, the clinician can opt to view all rules applicable to the patient.

Commonly used support and confidence thresholds [83-85] may not be suitable for our case, in which only a small percentage of patients are at high risk. We will adjust the support and confidence thresholds if the commonly used ones cannot produce enough meaningful association rules. By setting the thresholds low enough, we will produce meaningful rules at the expense of our clinicians spending time removing rules that make little or no clinical sense. Because existing predictive models give no suggestion on tailored interventions, we will regard Aim 2 successful if a nontrivial percentage (eg, ≥20%) of high-risk patients are covered by actionable rules.

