#### Performance Evaluation

The algorithm for explanations and suggestions will be evaluated in Aim 4.

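### The displayed rule confidence has no held-out estimate although the same figure selects and ranks the rules, so it is biased upward: negligibly at the example thresholds, by several points or more if support is cut far below 1%

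*Protocol article*

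**What the plan says.** Under Aim 2 the article separates prediction from explanation: "The rules used in the second model are mined directly from historical data rather than coming from the first model". The sample is described only in general terms: "In step 1, association rules are mined from historical data". Confidence is defined once: "Among all patients satisfying the rule’s left side, the percentage of patients at high risk reflects the rule’s accuracy". A rule must reach minimum support and minimum confidence, with 1% and 70% given as examples.

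For a patient flagged by the predictive model, matching rules are listed with actionable ones first, "each in descending order of confidence". About three are shown by default, and confidence is printed beside each: "We will list confidence and associated interventions, if any, next to each rule to help the clinician identify suitable tailored interventions".

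The thresholds may move: "We will adjust the support and confidence thresholds if the commonly used ones cannot produce enough meaningful association rules". The same paragraph calls Aim 2 successful if a nontrivial share of high-risk patients, for example 20% or more, is covered by actionable rules.

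On validation, Aim 1a (Accuracy Evaluation and Sample Size Justification) cross-validates the predictive models on the first 10 years and assesses the best of them on the 11th. Aim 2 says only: "The algorithm for explanations and suggestions will be evaluated in Aim 4".

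**The concern.** One statistic does three jobs: it admits rules, orders them, and is the number the clinician reads. When many noisy proportions are screened against a minimum and the largest are shown, those shown are partly there because chance pushed them up. Fewer patients per rule means more noise and a larger upward shift, so lowering the support threshold makes it worse.

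The predictive models are protected by the 11th-year hold-out. The rules are mined separately, and no such protection is described for them. At stake is a percentage that clinicians will use when choosing among interventions. Rules that pass the minimum by chance may also count towards the coverage criterion; the size of that effect has not been estimated.

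**Working it through.** The article gives no precision or error figure for rule confidence, so there is nothing of its own to reproduce.

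**Inputs from the article.** Example thresholds of 1% and 70%; about 27,000 children and 75,000 adults with asthma in the 11th year; three rules shown; support defined as the share of all patients who match the rule and are high risk. **Assumed.** A ten-year child pool of 10 × 27,000 = 270,000 independent records, and lowered thresholds, for which the article gives no values.

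**Step 1: noise in one rule.** At the minimum thresholds a rule rests on N × support high-risk patients and n = N × support / confidence matching patients. The standard error is SE = √(c(1 − c)/n).

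- Children, 1%/70%: 27,000 × 0.01 = 270 high-risk; n = 270/0.7 = 386; SE = √(0.21/386) = 2.3 points.
- Adults, 1%/70%: 750 high-risk; n = 1,071; SE = 1.4 points.
- Children, 0.1%/70%: 27 high-risk; n = 39; SE = 7.4 points.
- Children, 0.1%/30%: 27 high-risk; n = 90; SE = 4.8 points.

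**Step 2: bias after selection and ranking.** Simulation assumptions: 20,000 candidate rules; true confidences from a Beta distribution with mean half the minimum confidence and concentration 10 or 40; rules kept if they pass both thresholds; the top 3 by observed confidence taken from 30 applicable rules. Mean observed minus true confidence of those three, in points (a range covers the two concentrations):

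| Support / confidence | 27,000 | 75,000 | 270,000 |
|---|---|---|---|
| 1% / 70% | 0.9* | 0.3* | 0.1* |
| 0.1% / 70% | 9–20 | 3.3* | 0.9* |
| 0.1% / 30% | 3.1–7.0 | 1.1–2.7 | 0.3–0.7 |
| 0.05% / 30% | 5.8–12.3 | 2.2–5.2 | 0.6–1.5 |
| 0.02% / 30% | 13.1–21.6 | 5.4–11.0 | 1.5–3.8 |

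*Concentration 10 only; at 40 too few rules passed to give an estimate.

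**Step 3: could support really fall that low?** Suppose the model's score is binormal with AUC 0.80. The largest group with 70% at high risk then contributes support of 0.05% when 5% of patients are high risk, 0.27% at 8% and 0.54% at 10%. It reaches 1.06% at 8% with AUC 0.85, and 1.8% at 15% with AUC 0.80. A short rule built from the score's own features should rarely do better. With a small high-risk class, the pair 1%/70% is therefore often out of reach and one threshold has to give. If only confidence is lowered, the bias stays small. The article lets both fall and sets no floor.

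**Step 4: which repair works?** Mining on 270,000 records and re-estimating on 27,000, at supports of 0.1% to 0.03%, the top-three bias was:

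- displaying the mining value: about 0.1 to 1.4 points;
- dropping, ranking and displaying on the 11th-year value: about 2 to 8 points, because selection is repeated on a smaller sample;
- ranking on the mining years and displaying the 11th-year value: about 0.

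**The case against.** The article never says outright that displayed confidence comes from the mining data; it says historical data, and a condensed article may leave the sample to a fuller document. That is fair as a caution. But Aim 2 is specified down to tie-breaking, defines a single confidence, and is silent on a hold-out that Aim 1a spells out for the models. Aim 4 does not fill the gap: it simulates outcomes from intervention benefit, cost and uptake, and does not check confidence.

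The article lists safeguards: removal of redundant and noisy rules, a cap of about four items, restriction to features in the predictive model, and clinical review. The simulation does not model these. They shorten the list and may reduce the bias, but none re-estimates the confidence of the rules that remain.

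The larger figures need both low support and mining on a single year's patients. This stands: with ten pooled years and moderate support the effect is small.

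A reader might infer that clinicians will be shown an exaggerated risk for the patient in front of them. The documents do not support that. Confidence covers every patient matching the rule, whereas rules appear only for patients the model has already flagged, and the second model is meant to explain, not predict. In an illustrative logistic simulation, 21% of all matching patients were high risk against 31% of those also above the model's 95th percentile. The figure could therefore understate the flagged patient's risk.

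**Conclusion.** The point holds for the rule's own confidence. On the natural reading of Aim 2, the displayed value is optimistic because the same estimate selected and ranked the rule. The overstatement is under 1 point at the example thresholds, and also with 270,000 pooled records at 0.1% support and 30% confidence. It reaches several points or more only if support is taken far below 1%, chiefly when few patients are mined: about 3 to 7 points for 27,000 children at 0.1%/30%, and about 13 to 22 at 0.02%/30%. These sizes depend on the assumed number of rules, the spread of true confidences, 30 applicable rules per patient and independent records. Patients recurring across years would make the effective pool smaller than 270,000. This is a worthwhile and cheap correction, not a flaw that undermines Aim 2.

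**What to change.** State in Aim 2 that rules are mined, filtered, clinically reviewed and ranked on years 1-10 only, including any change to the support and confidence thresholds. Then compute each retained rule's confidence on the 11th-year data and display that value with its numerator and denominator. Do not drop or reorder rules on the 11th-year value, since that brings the selection bias back and also tunes the rules to the year on which Aim 4 estimates outcomes. Report coverage by actionable rules (the 20% criterion) among 11th-year high-risk patients, using the rules fixed from years 1-10.

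The cost is a recount on data already held. Low-support rules will rest on few 11th-year patients and show wide uncertainty: at 0.1%/30% a child rule has about 90 matching patients and a standard error near 5 points. Displayed values may also not fall in strict rank order, which a short note on the display can explain.

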#### Performance Evaluation

The algorithm for explanations and suggestions will be evaluated in Aim 4.

### Aim 3: Develop an Algorithm to Compute Optimal Thresholds for Risk Strata

In risk-stratified management, chronic disease patients are stratified into multiple levels [14,15]. This aim will compute the optimal thresholds for these levels that minimize total future cost of all patients factoring in the management programs’ costs. Total future cost implicitly reflects patient health outcomes, health care use, efficiency of care, and the management programs’ benefits. For instance, fewer hospitalizations usually lead to lower costs. The following discussion focuses on stratification based on predicted patient risk of experiencing a specific type of undesirable event (eg, hospitalization or emergency department visit). The case of stratification based on predicted cost or with more than one type of undesirable event can be handled similarly. Our discussion applies to any predictive model and is based on a fixed period in the future, such as the next 12 months.

#### Threshold Computation Algorithm

We will conduct quantitative analysis to determine the optimal management level for each risk percentile. We will proceed through the risk percentiles one by one, from the highest to the lowest. Given a risk percentile, we will compute for each management level the average future cost per patient in the percentile if patients in the percentile are put into the level. The level with capacity remaining in its management program and the lowest average future cost per patient will be chosen for the risk percentile.

More specifically, consider a risk percentile and an average patient whose predicted risk falls into the percentile. If the patient is enrolled in a management program, we estimate that the patient’s future cost will change by delta = the program’s cost – the program’s benefit gained by reducing undesirable events=*c*
_
*i*
_–*avg_n*
_
*e*
_**p***c*
_
*e*
_ compared with no enrollment. Here, *c*
_
*i*
_ is the program’s average cost per patient. Factors such as increased medication cost due to better medication adherence are included in *c*
_
*i*
_. *avg_n*
_
*e*
_ is the average number of undesirable events that a patient in the risk percentile will experience in the future. *p* is the percentage of undesirable events the management program can help avoid, reflecting the program’s benefit. *c*
_
*e*
_ is the average cost of experiencing the undesirable event once. *c*
_
*i*
_ and *p* can be obtained from statistics reported in the literature for the management program [39,88]. *avg_n*
_
*e*
_ can be obtained by making predictions on historical data and checking the corresponding statistics for the risk percentile. *c*
_
*e*
_ is obtained from statistics on historical data. The management level with the smallest delta is optimal for the risk percentile. If no statistics on *c*
_
*i*
_ and *p* of a management program are available in the literature, the clinician in our research team ([name]) will provide rough estimates based on experience. We will perform sensitivity analysis when choosing thresholds by varying the estimated values of *c*
_
*i*
_ and *p* to obtain the full spectrum of possible outcomes in Aim 4.

The preceding method performs an exhaustive search among all management levels for each risk percentile. In practice, we would expect *avg_n*
_
*e*
_ to decrease as the predicted patient risk of experiencing undesirable events becomes smaller. We will investigate using this property to reduce the search space when going through the risk percentiles one by one, from the highest to the lowest.

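### The one-pass rule in Aim 3 is not guaranteed to minimise total cost, and can fail when a less intensive program fills while a more intensive one still has room

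*Protocol article*

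**What the plan says.** The opening of Aim 3 sets a population-wide objective: "This aim will compute the optimal thresholds for these levels that minimize total future cost of all patients", with program costs counted. The Innovation subsection adds that the thresholds are meant to maximise return over the whole patient population and will beat heuristic ones.

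The Threshold Computation Algorithm subsection then gives the procedure. On order: "We will proceed through the risk percentiles one by one, from the highest to the lowest". On choice: "The level with capacity remaining in its management program and the lowest average future cost per patient will be chosen for the risk percentile". The criterion is delta = c_i − avg_n_e × p × c_e, where c_i is the program's cost per patient, avg_n_e the percentile's average number of undesirable events, and c_e the cost of one event. The factor p "is the percentage of undesirable events the management program can help avoid", one value per program. The subsection concludes: "The management level with the smallest delta is optimal for the risk percentile".

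On the scope of the search it says: "The preceding method performs an exhaustive search among all management levels for each risk percentile". It expects avg_n_e "to decrease as the predicted patient risk of experiencing undesirable events becomes smaller", and uses that expectation only to shorten the search.

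**The concern.** The objective is a minimum over all percentiles together, but the search covers only the levels open to one percentile at a time. Once capacity is limited, a slot given to one percentile is lost to those below it. The rule has no step that values the slot for later percentiles, revisits an earlier choice, or keeps the strata in order of risk.

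Two things are at stake. First, the optimality claimed for Aim 3 is not a property of the rule as written. Second, the output may not be a set of thresholds at all, although the Introduction describes a hierarchy in which higher predicted risk leads to more intensive care. Aim 4 uses the same algorithm to estimate outcomes and to compare computed with heuristic thresholds, so a shortfall would carry into those results.

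**Working it through.** Aim 3 states no numerical result, so there is no figure to reproduce. Write n for `avg_n_e`. Amounts are US dollars per patient, summed over equal-sized percentiles.

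**Inputs from the protocol.** The delta formula; one p per program and one c_e; n falling with risk. The Introduction says that case management can cost more than 5,000 per patient per year, can cut admissions and emergency visits by up to 30% to 40%, and typically enrolls 1% to 3% of targeted patients.

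**Assumed inputs.** c_e = 10,000. Case management (CM): cost 5,000, p = 0.4. Disease management (DM): cost 1,000, p = 0.2. Room for one percentile in each. No enrolment, with delta 0, always available. The values of n below.

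**Step 1: what a swap is worth.** Take two percentiles with n_H > n_L in two programs with p_high > p_low. Total program cost is the same either way round. Giving the higher p to the higher n therefore saves an extra (p_high − p_low) × (n_H − n_L) × c_e, which is always positive. Any inverted assignment is strictly beaten by its swap.

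**Step 2: deltas.**

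| n | DM: 1,000 − n × 0.2 × 10,000 | CM: 5,000 − n × 0.4 × 10,000 |
|---|---|---|
| 1.5 | −2,000 | −1,000 |
| 1.4 | −1,800 | −600 |
| 1.2 | −1,400 | +200 |

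**Step 3: apply the rule.**

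- n = 1.5 and 1.4. The top percentile takes DM (−2,000), which is then full. The next takes CM (−600). Total −2,600. The reverse gives −1,000 − 1,800 = −2,800. The gap of 200 equals (0.4 − 0.2) × (1.5 − 1.4) × 10,000, or 200/2,800 = 7% of the attainable saving. The higher-risk percentile sits in the less intensive level.
- n = 1.5 and 1.2. The top percentile takes DM (−2,000). For the next, CM would add 200, so it is not enrolled. Total −2,000. CM for the first and DM for the second gives −1,000 − 1,400 = −2,400. The gap is 400/2,400 = 17%.

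**Step 4: where the rule is exact.**

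- No limit binds: the total is a sum of separate terms, and each is minimised.
- Only the highest-p program is limited: its gain over the best unlimited alternative j changes with n at rate (p_top − p_j) × c_e, which is never negative. With n falling with risk, filling that program from the top gives its slots to the largest gains.

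**Step 5: dependence on the assumed capacity.** Give DM room for two percentiles and leave the rest unchanged. CM beats DM only if n × 0.2 × 10,000 > 4,000, that is n > 2. The rule puts both percentiles in DM and saves 2,000 + 1,800 = 3,800, or 2,000 + 1,400 = 3,400. Both are optimal, so the loss and the inversion disappear.

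**Step 6: larger examples, all with assumed inputs.** Take 100 percentiles, CM (5,000, p = 0.40, room for 3), DM (1,000, p = 0.25, room for 5), and n × c_e falling about 3% per percentile.

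- With a top value of n × c_e from 15,000 to 26,000, the rule fills DM first and then uses CM for two or three lower percentiles. The optimum is CM for the top three, then DM for five. The loss is 5.7% falling to 4.1% of the attainable saving.
- At 30,000 and 40,000 the rule equals the optimum. CM is preferred above 4,000/0.15 = 26,667.

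Random scenarios were also compared with the exact capacitated assignment: 3,000 per row, 30 risk groups, four programs plus no enrolment, p from 0.02 to 0.40, costs from 10 to 5,000.

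| Limited programs | Suboptimal | Inverted | Median loss when suboptimal | Largest loss |
|---|---|---|---|---|
| None | 0% | 0% | – | – |
| Most intensive only | 0% | 0% | – | – |
| Two most intensive | 10% | 8.9% | 0.4% | 5.2% |
| All four | 48% | 37% | 1.6% | 23.5% |

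**The case against.** The strongest reply is that the only capacity the protocol quantifies is that of case management, the most intensive program, and under that limit alone the rule is exact (Step 4). The examples given for lower levels, such as reminder calls, monitoring tools and mailed materials, carry no stated cap. This stands. A reader might infer that the rule fails whenever capacity is limited, that the thresholds will in fact be suboptimal, or that the rule should be kept only for programs without limits. The documents support none of these.

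It is also fair to say that the loss may be small beside the uncertainty in c_i and p, which may be rough clinical estimates; that a shortfall would count against the new method in the comparison with heuristic thresholds; and that clinicians make the final decisions. A reader might likewise infer that Aims 3 and 4 necessarily understate the achievable saving, but that too holds only under the failing capacity pattern.

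What the reply does not remove is the gap between objective and rule. The rule applies the capacity condition to every level, not to case management alone. The planned sensitivity analysis varies c_i and p, not the assignment method, so it would not reveal the problem. In the first example of Step 3 the better assignment is the conventional ordering by risk, so the algorithm can lose to a plain hierarchy, contrary to the Innovation subsection.

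**Conclusion.** The point holds in a limited form. The rule is not guaranteed to deliver the minimum that Aim 3 promises. One counterexample under the plan's own delta is enough to show this, and when it fails the result may not be expressible as risk thresholds. The failure requires a less intensive program to run out while a more intensive one still has room.

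The size is not determined by the documents. With assumed inputs it ran from zero to 17% in the worked examples, and the typical loss in the random scenarios was small even where the rule was suboptimal. The argument rests on equal-sized percentiles, one p per program and one c_e, as the plan's formula implies. The exactness results for a limited top program also need n to fall with risk. This is a correction to make before the algorithm is coded. It does not touch Aim 1.

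**What to change.** Replace the one-pass rule by a joint assignment over all percentiles. Minimise the sum of delta over percentiles and levels, with exactly one level per percentile and no level above its capacity. Equivalently for this purpose, search over ordered cut-points under the same capacities, which guarantees that the output is a set of thresholds.

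The change takes a few lines of code and some rewording, and needs no new data. Ordering costs nothing when n falls with risk, as the protocol expects, because by Step 1 some optimal assignment is then ordered. Where observed n is not monotone, ordered cut-points may cost slightly more than the unconstrained minimum. That is the small downside, and both totals can be reported.

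If the one-pass rule is kept, the plan should state when its thresholds are optimal: no binding limit, or a limit on the most intensive (highest-p) program only, with n falling with risk. It should not claim optimality outside those conditions.
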